## Abstract

Anti-neutrophil cytoplasmic antibody (ANCA) associated vasculitis (AAV) is a chronic, relapsing-remitting condition associated with increased morbidity. Previous research has shown patients with AAV report high levels of fatigue, pain, depression and anxiety. Over recent years successful work has been carried out to improve clinical outcomes, resulting in reduced mortality and end stage kidney disease (ESKD). Despite this, little work has been done to better understand the role of the patient within this condition. The prevalence of AAV is increasing and to date, there is a shortage of specific tools that assess and measure key features relating to patient reported outcomes (PROs). This protocol details how we can better understand the lived experiences of those with AAV through the development of a disease specific, patient reported outcome measure (PROM), to be used in clinic practice. This will allow us to recognise and validate PROs and the impact the disease and its treatment has on patients’ health related quality of life (HRQoL). In addition, we aim to identify potential differences in PRO’s between demographics, organ involvement and treatment subgroups in AAV as well as outcomes relating to the patient experience. Patients from a single centre in the UK will be recruited to take part in the exploratory qualitative study which will include focus groups and semi-structured interviews. The inclusion criteria comprise anyone with a diagnosis of AAV and willing to participate, including those who have active or relapsing disease, those are economically active, unemployed, retired and patients receiving renal replacement therapy. The aim of the project is to identify key issues patients experience in relation to their disease and its management and how these can be better assessed in a new PROM developed for use in the clinic setting. This will enable better delivery of individualised care and inform shared decision making, while also serving as a platform for future research looking at PROs in other glomerulonephritides.

## Introduction

Anti-neutrophil cytoplasmic antibody (ANCA) associated vasculitis (AAV) is a complex multisystem disorder that is associated with a high degree of morbidity [1, 2]. As a result, AAV leads to poor health status and health related quality of life (HRQoL), as well as a high burden of pain, fatigue, depression and anxiety [3–6]. Over recent years multiple tools have been developed to aid clinicians in their assessment of patient’s disease, so as to influence decision making and guide treatment. Tools such as the Birmingham Vasculitis Activity Score (BVAS) [7] and Vasculitis Disease Index (VDI) [8] have been validated to help predict clinical outcomes and determine those at highest risk of relapse or adverse events. Yet little work has been done comparatively to understand patients’ perspectives and the impact of AAV on them as individuals.

When considering patient reported outcomes (PROs), patient reported outcome measures (PROMs) are tools that assess patients perspective of health and treatment, encompassing subjective assessments of disease burden, activities of daily living, functionality, psychological health and HRQoL [9]. Patient-reported experience measures (PREMs) are also helpful when determining factors important to patient and address the patients experience of quality and satisfaction of care. Over recent years many PROMs have been developed for a variety of health conditions and are increasingly used as research outcome, as well as an overall indicator for good quality and effective patient care [10]. A recent systematic review of PROMs used in AAV has shown generic measures of PRO are useful in measuring significant changes but may not be sensitive to patients with particular symptoms or unique issues related to their condition [11]. The Short Form 36 (SF-36) [12] was the most widely used generic PROM but does not fully encompass all aspects of AAV or disease related issues that are important to patients [13–15]. With the exception of Robson *et al*. AAV-PRO [16], little research has been done to develop validated disease specific tools for patients living with AAV.

The 29-item AAV-PRO is the only disease specific tool currently available for the use in AAV and includes domains relating to systemic and organ specific symptoms, treatment related side effects, psychological and social well-being, impact on physical function and concerns about the future [6, 16]. The tool has been validated globally and translated into many different languages. It has demonstrated good face and construct validity and reliability [16, 17]. However, as with any tool there are recognised limitations, such as its ability to measure and assess changes over time. The 4-week assessment period has the potential to under report both transient and chronic symptoms, whilst limited facets address the economic impact on HRQoL. Furthermore, the tool was designed for application in clinical research and trials and its usability or suitability for real-time use in routine, clinical practice may be limited.

This study has been designed to better recognise the gap that exists in evidencing and understanding the key factors that are important to patients living with AAV. We aim to develop a tool that can be used in clinical practice to help aid patient and clinicians understanding and track changes in HRQoL over time. At an individual level, better understanding of the disease burden may facilitate a holistic, patient-centred approach to clinical decision making and identify those patients at risk or vulnerable to treatment related toxicities or relapsing disease. On a wider and longer-term level, these outcomes can be used to compare treatments, provide insight into inequalities, inform care pathways and allow for service enhancements (Fig 1). Here we present a protocol for this exploratory qualitative study which includes details on the methodology, data analysis and ways in which we aim to improve PROs and HRQoL as a result.

**Fig 1 pone.0298796.g001:**
[figure not shown]
Short-, mid- and long-term benefits that Patient Reported Outcome Measures (PROMs) offer to improving patient care. MDT; Multidisciplinary Team, PPI; Patient and Public Involvement, PROMs; Patient Reported Outcome Measures, ePROMs; Electronic Patient Reported Outcome Measures, RCT; Randomised Control Trial.

## Materials and methods

### Research aims and objectives

The primary outcome for this study is to develop a real-world understanding of how AAV and its treatment impacts PRO’s (Fig 2). To do this we will explore individuals’ lived experience of AAV and understand the key factors which are important to them, so as to incorporate this into a disease-specific PROM. This can then become a tool that can accurately and reliably measure AAV patients’ HRQoL for use in a clinical setting. This will take into account how HRQoL changes with time, relapse and disease remission, as well as looking at the impact of immunosuppressive therapies, including glucocorticoids (GCs).

**Fig 2 pone.0298796.g002:**
[figure not shown]
Protocol for study setup and process. AAV; Anti-neutrophil cytoplasmic antibody (ANCA) associated vasculitis, HRQoL; health related quality of life, PROM; patient reported outcome measure; REC; Research Ethics Committee, SRQR; standards for reporting qualitative research.

### Significance statement

Despite AAV being a rare disease, its prevalence is increasing and more people are living with AAV as a chronic diagnosis [18]. To date, the primary focus of clinical research trials in AAV have been on patient and renal survival. More recently, in particular pharmaceutical trials, HRQoL questionnaires such as the SF-36 have been included as secondary outcome measures. Whilst these studies have identified reduced HRQoL in patients with AAV, tools specifically focusing on the impact of the disease process, treatment related toxicity and changes over time are still lacking [6, 15, 19]. The existing literature identifies significant burden of illness perception and poor health in those living with AAV [20–22]. Economic, social, and reproductive health have also been significantly affected and improvements in individualised management are required [16, 23, 24]. Addressing PROs and identifying key themes which can potentially be improved is essential for personalised and comprehensive clinical care, necessitating disease-specific tools to address unique adverse effects related to AAV and its management. Integrating PROMs into routine clinical care will further enhance the patient experience and provide a framework for shared decision making. This is especially important given the complexity, multi-organ involvement and relapsing nature of AAV.

### Study setting and design

The study will be conducted at a single centre; Royal Preston Hospital, Lancashire, UK. This study which will consist of two parts:

**Phase I.** Development of a AAV specific PROM tool. Using qualitative research methods, 15–20 patient participants will be invited to explore their experiences of living with AAV and what HRQoL means to them. Focus groups will be conducted using a semi-structured topic guide and common themes already identified from a systematic review of the existing literature will be used as prompts. Within the focus group there will be a section looking at the current generic and disease specific PROMs available and the advantages and disadvantages of each tool in relation to the patient’s own experience. For the purpose of time, patients will be sent details on the existing tools for their review ahead of the focus group. The participants will be asked to discuss what a ‘desirable’ AAV specific tool should include and how it could be developed for use in the clinical setting. Patients will be asked about their experience in relation to the care and treatment they received which may inform future work looking at PREMs for those with AAV.

Key themes raised and repeated will be incorporated to develop a disease specific PROM. Two or three participants from the initial focus group will be asked to comment on the proposed wording/presentation of the items/scale. Following this a select number of participants (n = 5–10) will be asked to take part in a ‘think aloud’ interview. The purpose of this is to understand how patients feel when completing the tool and ensure that the tool is acceptable and meaningful to patients. They will be asked to comment on the wording, clarity, acceptability, ease of completion and aesthetics of the tool. Subsequently further refinements will be made if needed to create a final version.

**Phase II.** Is the application and validation of the PROMs tool. In order to fully complete psychometric evaluations, other data including clinical data from medical records and treatment information may be needed to fully correlate with the PROMs tool. Which other data we collect will be determined by what is established from Phase I where we establish what patient’s value most when considering HRQoL. The protocol estimates a sample size of 200–250 participants to ensure adequate statistical power, following the established principle of 10 people per item included assuming a maximum of 20–25 items included in the final version [25].

The newly developed PROM will be sent to patients either by email or given during routine clinic appointments. The tool will be a pen and paper survey which is self-completed by patients. There will be deposit boxes in clinic or the option of email return of scanned copies (including photos taken using smart phone technology or similar) and patients will be encouraged to discuss their outcomes with healthcare professionals in clinic if they wish to. Statistical analyses will be used to assess the psychometric properties of the tool and test the structure of the questionnaire. Psychometric properties will include: construct validity, criterion validity, floor and ceiling effects, sensitivity to change and internal construct reliability. A test- retest analysis will be carried out 1 month following the initial questionnaire. The initial questionnaire will have an option box asking if patients are happy to be contacted again for further follow up questions. Of those that agree by ticking this box, a sub sample (n = 100) of randomly selected participants will be identified and asked to complete the test survey again with a specific yes / no question asking if anything substantial had changed in relation to their illness or treatment.

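### Phase II promises sensitivity to change, but its only fixed repeat is a 1-month retest in 100 people whose yes/no change item has no direction

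*Protocol article*

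**What the plan says.** In the protocol article, the Phase II part of 'Study setting and design' commits to a list of measurement properties: "Psychometric properties will include: construct validity, criterion validity, floor and ceiling effects, sensitivity to change and internal construct reliability".

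The same section describes the data collection. Each participant completes the tool once. The one repeat is set out as follows: "A test- retest analysis will be carried out 1 month following the initial questionnaire". It is limited to people who agree to further contact, from whom "a sub sample (n = 100) of randomly selected participants will be identified". The second form carries the only committed indicator of change, a single item covering both illness and treatment: these people are "asked to complete the test survey again with a specific yes / no question asking if anything substantial had changed". Clinical and treatment data from records are mentioned as something that may be needed, with the choice left until after Phase I.

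The sample size is justified separately: "The protocol estimates a sample size of 200–250 participants to ensure adequate statistical power", on the rule of "10 people per item included assuming a maximum of 20–25 items included in the final version".

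Change over time is also among the reasons for building the tool. The Introduction names as a limitation of the existing disease-specific instrument points "such as its ability to measure and assess changes over time". 'Research aims and objectives' says of the new tool: "This will take into account how HRQoL changes with time, relapse and disease remission".

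**The concern.** Test-retest reliability and sensitivity to change need different patients. Reliability is estimated in people whose condition has stayed the same. Responsiveness is estimated in people who changed, in a known direction. A single short-interval repeat in a random sub-sample, with a yes/no question, fits the first purpose: the people answering yes can be set aside. For the second it leaves whatever number happen to answer yes, with improvement and deterioration in one group, and illness change mixed with treatment change.

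At stake is one listed property that bears on a stated purpose of the tool. Once the retest forms are back, an analysis plan can add a responsiveness statistic, but it cannot recover from a yes/no answer which way the patient moved.

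**Working it through.** **1. The plan's own figure.** 10 people per item × 20 items = 200, and 10 × 25 = 250. The stated 200-250 reproduces. It is a rule based on the number of items and does not address change. No derivation is given for the retest sample of 100, so there is nothing to reproduce there.

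**2. How many people will have changed?** The article gives neither the share of the 100 who return the retest nor the share who answer yes. Both are assumed here.

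Changed n = 100 × return × share changed.

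- Widest range (60-100% return, 5-30% changed): 100 × 0.60 × 0.05 = 3, up to 100 × 1.00 × 0.30 = 30.
- Middle range (60-80% return, 10-20% changed): 100 × 0.60 × 0.10 = 6, up to 100 × 0.80 × 0.20 = 16.

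**3. What those numbers can show if everyone moves the same way.** The effect is the standardised response mean (SRM), the mean change divided by the SD of change. The value 0.5 is illustrative. The test is a paired t-test at two-sided 5%, with noncentrality SRM × √n. The approximate 95% half-width is 1.96 × √(1/n + SRM²/(2n)) at SRM = 0.5.

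| Changed n | Power at SRM 0.5 | Smallest SRM with 80% power | 95% half-width |
|---|---|---|---|
| 6 | 17% | 1.43 | 0.85 |
| 12 | 35% | 0.89 | 0.60 |
| 16 | 46% | 0.75 | 0.52 |
| 30 | 75% | 0.53 | 0.38 |

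At the favourable end, 30 people all moving one way, power is still a little under 80%. A larger effect is easier to see: at SRM 0.8, n = 16 gives about 85%.

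**4. What mixing directions does to the signed mean.** Suppose each changed person moves by d = 0.5 SD, a share q improves, and individual variation has SD 1. Then the mean is d(2q − 1), the SD is √(1 + 4d²q(1 − q)), and the observed SRM is their ratio.

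- q = 1.0: 0.50 / 1.00 = 0.50
- q = 0.8: 0.30 / 1.077 = 0.28
- q = 0.7: 0.20 / 1.100 = 0.18
- q = 0.5: 0 / 1.118 = 0.00

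The yes/no item does not record q, so a reader of the results could not tell a tool that fails to respond from one that responds in both directions.

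**5. What a directional item would give.** In the best case above, 30 changed people split evenly leave 15 in each direction. The half-width is 1.96 × √(1/15 + 0.25/30) = 0.54, and power at SRM 0.5 is 44%. Direction becomes known, but precision stays low, so the result would be exploratory.

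**The case against.** Several points on the other side are fair.

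- **Some estimate is possible.** Absolute change, or the spread of change, can be compared between yes and no responders without cancellation. Clinical data chosen after Phase I could supply a directional anchor. A reader might infer that sensitivity to change cannot be estimated at all, or that a responsive tool would be bound to look unresponsive. The article supports neither. What stands is that no directional anchor is committed to, and that an absolute-change comparison cannot show that the tool tells improvement from deterioration.
- **Change over time is not the whole purpose.** A reader might infer that the study fails at its main claim. The primary outcome is a real-world understanding of how the disease and its treatment affect patient-reported outcomes. The Introduction also cites the recall period, thin economic content and limited clinic usability as reasons for a new tool. The statement in 'Research aims and objectives' can be read as an aim for the tool's content, which Phase I could serve, so it need not be removed.
- **Naming a statistic can be left to the analysis plan.** This is accepted. That the analysis text names no responsiveness method is not part of this point, which rests on what is collected.
- **The rates are assumed.** This is also accepted, which is why ranges are shown. The conclusion about direction depends on none of them.

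**Conclusion.** The point holds in a limited form. Phase II commits to assessing sensitivity to change, but the repeat measurement it fixes is suited to reliability and carries no information on the direction of change. Under assumed return of 60-100% and a changed share of 5-30%, about 3 to 30 people would report a change. Power for a standardised change of 0.5 is 17-46% with 6 to 16 people and about 75% with 30, in each case only if all move the same way. With mixed directions the signed mean shrinks further. The return rate, the changed share and the effect size are all assumptions; the missing direction is read directly from the article.

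The other listed properties, namely validity, internal reliability, and floor and ceiling effects, are untouched. This is a mismatch between one promised property and the data fixed for it, best settled before the retest form is finalised.

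**What to change.** Replace the yes/no item on the retest form with a directional, graded global rating of change, from much better through same to much worse. Use the 'same' group for the test-retest intraclass correlation. Report the better and worse groups separately as exploratory responsiveness, with confidence intervals.

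If that is not wanted, remove sensitivity to change from the Phase II list in 'Study setting and design' and state that responsiveness is left to later work.

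A further completion at a routine clinic visit is optional. It needs linked follow-up and dated clinical data, and its yield is uncertain. For illustration, 50 changed people would take 50 / 0.20 = 250 completed repeats if 20% change, or 50 / 0.10 = 500 if 10% change.

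The cost of the main fix is one reworded item, a minor amendment, and a more modest claim about responsiveness. Removing the property from the list costs almost nothing beyond giving up that claim.

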## Conclusion

To date, there is a lack of disease specific tools to assess and measure PROs in people living with AAV. Existing PROMs are not without limitations when evaluating the impact of AAV and its treatments on patients’ physical, social and psychological well-being, as well as the influence of demographics, organ involvement and specific therapies on HRQoL. This protocol aims to enhance our understanding of ways in which to quantify key issues patients experience in relation to their disease and its management. Consequently, it will allow for better delivery of care, individualisation of therapy and shared decision making.

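### The 1-month retest asks only about change in illness or treatment, although the tool is to measure multi-dimensional HRQoL; if the answer defines the stable patients, the retest ICC is biased down, probably modestly

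*Protocol article*

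**What the plan says.** Under Study setting and design, Phase II, the protocol article states: "A test- retest analysis will be carried out 1 month following the initial questionnaire". From those who agree to further contact, "a sub sample (n = 100) of randomly selected participants will be identified", and they repeat the survey with "a specific yes / no question asking if anything substantial had changed in relation to their illness or treatment". This is the only item on stability that the article describes. It does not say how the answer enters the analysis. Under Transcription and analysis, intra-class correlation is listed among the techniques for validity and reliability, without a target value or a definition of the retest set.

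The construct is set out elsewhere. Research aims and objectives calls for a tool that measures HRQoL in these patients. Transcription and analysis speaks of a multi-dimensional HRQoL construct. The Introduction faults the existing disease-specific tool for thin economic content. The Significance statement says "Economic, social, and reproductive health have also been significantly affected", and the Conclusion refers to effects on "physical, social and psychological well-being". The actual domains and items are left to Phase I.

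**The concern.** A test-retest coefficient estimates reliability only in people who are stable on what is being measured. Here the stability marker covers clinical status and therapy, while the measured quantity is HRQoL. A patient whose work, finances, family situation or mood changed during the month, for reasons they do not connect with the vasculitis, can answer no even though their scores have moved. If a no answer places them in the stable set, their real change is counted as error and reliability is understated.

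The missing information is never collected, so no later analysis can recover it. The same section lets Phase I findings decide which other Phase II data are collected, but fixes the scope of the retest question in advance, whatever domains patients raise.

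**Working it through.** **The plan's own figure.** The article says: "The protocol estimates a sample size of 200–250 participants to ensure adequate statistical power", based on "10 people per item included assuming a maximum of 20–25 items included in the final version". 10 × 20 = 200 and 10 × 25 = 250, so the figure reproduces. It does not bear on the retest question.

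**Inputs.** From the protocol: one month between completions and 100 patients asked. Assumed, because the protocol gives none of them:
- R, the ICC in truly stable patients: 0.80, 0.85 or 0.90.
- f, the share of patients treated as stable who had an unrecorded true change: 10%, 20% or 30%.
- d, the root-mean-square size of that change in baseline SD units: 0.5 or 0.8, plus two mixed cases below.

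**Model.** The baseline score has variance 1, of which R is true-score variance. Two versions bracket how change acts.
- Change added independently of the baseline true score: ICC = R / (1 + f·d²/2).
- Total variance unchanged at retest: ICC = R − f·d²/2.

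**Results** (first version / second version):

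| R | d | f = 10% | f = 20% | f = 30% |
|---|---|---|---|---|
| 0.80 | 0.5 | 0.790 / 0.788 | 0.780 / 0.775 | 0.771 / 0.763 |
| 0.80 | 0.8 | 0.775 / 0.768 | 0.752 / 0.736 | 0.730 / 0.704 |
| 0.90 | 0.5 | 0.889 / 0.888 | 0.878 / 0.875 | 0.867 / 0.863 |
| 0.90 | 0.8 | 0.872 / 0.868 | 0.846 / 0.836 | 0.821 / 0.804 |

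Example: R = 0.80, d = 0.5, f = 30% gives 0.80 / (1 + 0.30 × 0.25 / 2) = 0.80 / 1.0375 = 0.771, and 0.80 − 0.0375 = 0.763 to rounding. At d = 0.5 the loss therefore runs from about 0.01 to 0.04.

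**Change with a mean m and spread s.** Here d² = m² + s², and the first version applies, with R = 0.85.
- m = −0.3, s = 0.5: d = √0.34 ≈ 0.58. ICC = 0.836, 0.822, 0.809 for f = 10%, 20%, 30%, a loss of 0.014 to 0.041.
- m = −0.5, s = 0.8: d = √0.89 ≈ 0.94. ICC = 0.814, 0.781, 0.750, a loss of 0.036 to 0.100. For f = 10%: 0.85 / (1 + 0.10 × 0.89 / 2) = 0.85 / 1.0445 = 0.814.

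**Sampling error.** By Fisher's z with standard error 1/√(n − 1.5), the 95% interval at n = 100 is 0.717 to 0.861 around 0.80 and 0.855 to 0.932 around 0.90. All the 0.5 SD results lie inside these intervals.

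**The case against.** The strongest reply is that the question fits the construct. The aims, the topic guide and the Conclusion all present HRQoL as affected by the disease and its therapy. If items ask about problems caused by the vasculitis, a bereavement or an unrelated change at home should barely move the score. The question is also phrased loosely enough that someone who lost work because of the disease could answer yes. This largely stands, and it makes the bias conditional on item wording. It does not remove it: the article commits to no such wording, and its stated aim is to measure HRQoL itself.

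Several stronger readings are tempting but not supported:
- A reader might infer that the plan counts every no as stable. The article never says so, and may properly leave the analysis set to a fuller document.
- A reader might infer that sound social, economic or psychological items will look unreliable and be dropped. Those domains are not fixed before Phase I, the calculation above is not domain-specific, and no section says items are removed on retest results. Refinement to a final version is described after the think-aloud interviews.
- A reader might infer that clinic discussion spoils the retest, since "patients will be encouraged to discuss their outcomes with healthcare professionals in clinic if they wish to". That discussion is optional and its effect cannot be sized from the article. Any treatment change arising from it would already be caught by the question.

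It is also fair to say that a loss of 0.01 to 0.04 would be hard to see with 100 pairs. Unlike sampling error, though, it is systematic and does not shrink with more patients.

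**Conclusion.** The mismatch in scope is on the page: the question covers illness and treatment, and the tool covers HRQoL. If the answer selects the stable patients, the ICC is biased downward. The likely size is modest, about 0.01 to 0.04 for 10–30% unrecorded changers with a change of roughly 0.5 SD. It reaches about 0.07 to 0.10 only under severe assumptions, such as 30% changers at 0.8 SD. All of these shares and sizes are assumed. The article does not support calling the bias established or large. This is a cheap improvement of minor weight, worth making because the missing information cannot be recovered after data collection.

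**What to change.** Keep the illness/treatment question and add one global yes/no item to the retest form, for example: *Since you first filled in this questionnaire, has your overall quality of life or your life circumstances (work, money, home, family, mood) changed substantially?* A bare list of life events would serve less well: it could miss a change in mood and would exclude patients whose HRQoL did not move.

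State in the plan how the answers define the retest set. Estimate the retest ICC in patients who answer no to both questions, and report the ICC based on the illness/treatment question alone as a sensitivity analysis.

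The cost is one tick-box, one extra estimate and somewhat fewer stable pairs, some of them from patients whose scores would not have moved. As an illustration, a fall from 100 to 70 pairs at an ICC of 0.80 changes the 95% interval from 0.717–0.861 to 0.697–0.871, a width of 0.174 instead of 0.144.
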